## Abstract

**Background:**

The routine implementation of sternal precautions to prevent sternal complications that restrict the use of the upper limbs is currently worldwide practice following a median sternotomy. However, evidence is limited and drawn primarily from cadaver studies and orthopaedic research. Sternal precautions may delay recovery, prolong hospital discharge and be overly restrictive. Recent research has shown that upper limb exercise reduces post-operative sternal pain and results in minimal micromotion between the sternal edges as measured by ultrasound. The aims of this study are to evaluate the effects of modified sternal precautions on physical function, pain, recovery and health-related quality of life after cardiac surgery.

**Methods/design:**

This study is a phase II, double-blind, randomised controlled trial with concealed allocation, blinding of patients and assessors, and intention-to-treat analysis. Patients (n = 72) will be recruited following cardiac surgery via a median sternotomy. Sample size calculations were based on the minimal important difference (two points) for the primary outcome: Short Physical Performance Battery. Thirty-six participants are required per group to counter dropout (20%). All participants will be randomised to receive either standard or modified sternal precautions. The intervention group will receive guidelines encouraging the safe use of the upper limbs. Secondary outcomes are upper limb function, pain, kinesiophobia and health-related quality of life. Descriptive statistics will be used to summarise data. The primary hypothesis will be examined by repeated-measures analysis of variance to evaluate the changes from baseline to 4 weeks post-operatively in the intervention arm compared with the usual-care arm. In all tests to be conducted, a *p* value *<*0.05 (two-tailed) will be considered statistically significant, and confidence intervals will be reported.

**Discussion:**

The Sternal Management Accelerated Recovery Trial (S.M.A.R.T.) is a two-centre randomised controlled trial powered and designed to investigate whether the effects of modifying sternal precautions to include the safe use of the upper limbs and trunk impact patients’ physical function and recovery following cardiac surgery via median sternotomy.

**Trial registration:**

Australian and New Zealand Clinical Trials Registry identifier: ACTRN12615000968572. Registered on 16 September 2015 (prospectively registered).

**Electronic supplementary material:**

The online version of this article (doi:10.1186/s13063-017-1974-8) contains supplementary material, which is available to authorized users.

## Background

Cardiac surgery via a median sternotomy has been performed in over 1 million cases worldwide [1, 2] because it provides the best clinical outcome for patients with multiple-vessel disease and co-morbidities [3–7]. Despite these advantages, the incidence of sternal complications has remained relatively unchanged for the last 2 decades and is reported to be between 0.4% and 8% worldwide [8–11]. Sternal complications include dehiscence, wound infection, sternal instability/non-union and mediastinitis [11]. These complications are associated with significant morbidity and prolonged hospital length of stay, and they contribute to increased health care costs [8, 11, 12].

To prevent sternal complications, the routine implementation of sternal precautions that place restrictions on the use of the upper limbs and trunk commences immediately post-operatively. These precautions are used worldwide, although they are applied for variable periods of time (4 weeks to 3 months) post-operatively [8, 13, 14]. The evidence to support sternal precautions is limited to cadaver and replica bone model studies [15, 16]. In a foundational study, McGregor et al. found that a force of 220 ± 40 N was required to attain 2-mm distraction between sternal edges in the lateral direction, 263 ± 74 N in the anteroposterior direction and 325 ± 30 N in the rostrocaudal direction [16]. This prompted a recommendation to discourage the bilateral use of the upper limbs because this was thought to increase the distractive forces at the sternal edges [16]. From the outset, health care professionals, including surgeons, nurses and physiotherapists, routinely reinforce sternal precautions in their clinical practice. However, a recent study demonstrated that upper limb and trunk tasks cause only minimal micromotion of the sternal edges (<2 mm) as measured by real-time ultrasound, and this was the case for all tasks, including bilateral and unilateral arm elevation [17]. On the basis of these findings, restricting the use of the upper limbs and trunk in an attempt to prevent excessive sternal motion may be overly cautious. Sternal precautions in the form of physical restrictions may delay recovery, prolong return to function and delay hospital discharge, and as such may be overly restrictive [8, 18, 19].

Upper limb and trunk exercises are encouraged as part of post-operative care to promote recovery and return of function [8, 13, 14, 18]. Sturgess et al. found that exercises of the trunk and upper limb significantly reduced sternal pain during the first 6 weeks post-operatively [20]. The prescription of such exercises alongside sternal precautions poses a clinical dilemma because they contradict each other [8, 13, 44]. Further, physical activity and upper limb exercises may be imperative for healing and remodelling of bone, which responds to loading [8, 21].

### Trial objective and hypothesis

The primary aim of this study is to evaluate the effectiveness of a program of modified sternal precautions on physical function compared with standard care sternal precautions following cardiac surgery via a median sternotomy at 4 weeks post-operatively. We hypothesise that those receiving the modified sternal precautions will have improved physical function at 4 weeks post-operatively compared with participants receiving standard care precautions. The secondary aims are (1) to evaluate the effectiveness of modified sternal precautions compared with standard care on sternal pain and discomfort, kinesiophobia and health-related quality of life (HRQoL) at 4 weeks and 3 months post-operatively, as well as on physical function at 3 months post-operatively; (2) to measure participants’ adherence to sternal precautions; and (3) to explore whether demographic factors, co-morbidities and/or pre, peri- and post-operative risk factors are associated with the development of post-sternotomy complications. This will be an exploratory analysis which may identify trends of predictors reported in the literature [11].

## Methods/design

The methods are reported in accordance with the Standard Protocol Items: Recommendations for Interventional Trials (SPIRIT) guidelines for clinical trials [22] (*see* Additional file 1, Table 1) and the Template for Intervention Description and Replication (TIDieR) reporting of interventions [23] (*see* Additional file 2).

**Table 1 Tab1:** Additional file World Health Organisation trial registration data set for S.M.A.R.T.

Data category	Information
Primary registry and trial identifying number	Australian New Zealand Clinical Trials Registry number: ACTRN12615000968572
Date of registration in primary registry	16 September 2015
Secondary identifying numbers	N/A
Trial protocol version	This is the version 3 of the protocol and was enacted November 2015
Source(s) of monetary or material support	Nil
Primary sponsor	Nil
Secondary sponsor	Nil
Contact for public queries	[name]
Contact for scientific queries	[name]
Public title	Sternal Management Accelerated Recovery Trial (S.M.A.R.T.): The efficacy of modified sternal precautions on improving physical function in patients following cardiac surgery via a midline sternal incision.
Scientific title	A randomised controlled trial of the efficacy of modified sternal precautions versus standard care on improving physical function following cardiac surgery via a median sternotomy
Countries of recruitment	Australia
Health condition(s) or problem(s) studied	Cardiac surgery via a median sternotomy
Intervention(s)	Active comparator: Placebo comparator:
Key inclusion and exclusion criteria	Ages eligible for study: ≥18 years Sexes eligible for study: both Accepts health volunteers: No Inclusion criteria: all adults underwent elective cardia surgery involving a median sternotomy Exclusion criteria: 1. Unable to understand verbal instructions in English. 2. Residing outside Melbourne metropolitan area (i.e., 52-km radius).
Study type	Type: Investigator initiated, interventional, non-pharmacological, pragmatic, study Allocation: concealed randomisation Intervention model: parallel assignment Masking: patient and assessor blinded Primary purpose: prevention
Date of first enrolment	16 September 2015
Target sample size	72
Recruitment status	Completed recruitment on 16 November 2016
Primary outcome(s)	Short Physical Performance Battery (SPPB)
Key secondary outcomes	2. Patient-identified cardiac pain using numeric and visual prompts, Short Form McGill Pain Questionnaire 2 (SF-MPQ-2), Functional Difficulties Questionnaire (FDQ), grip strength, Tampa Scale of Kinesiophobia shortened version (TSK-11), Medical Outcomes Study 36-item Short Form Health Survey (SF-36v2), Global Rating of Change Scales

*S.M.A.R.T.* Sternal Management Accelerated Recovery Trial

### Trial design

The Sternal Management Accelerated Recovery Trial (S.M.A.R.T.) is a phase II, prospective, parallel-group, concealed-allocation, randomised (1:1), controlled, patient- and assessor-blinded clinical trial powered for superiority and being conducted at two tertiary hospitals. Participants will be randomised to participate in the trial if they meet the eligibility criteria, give informed consent and have completed baseline measurement testing performed by a blinded assessor in an outpatient setting. Participants will be informed that they will be randomised to receive either standard or modified sternal precautions before hospital discharge and will be allocated to one of two groups: (1) the control group (standard care) or (2) the intervention group (modified sternal precautions). In addition, participants are asked to provide a global rating of change in physical function using a numeric scale (Global Rating of Change Scales [GRC]).

### Trial setting

The trial will be carried out at two tertiary hospitals: Royal Melbourne Hospital (RMH), and Melbourne Private Hospital (MPH), both located in the state of Victoria, Australia. RMH is a government-funded, university-affiliated teaching hospital, and MPH is a private hospital located adjacent to RMH. This study is being conducted at two major metropolitan hospitals (one private and one public), and the findings can be generalised to both private and public health care settings. Most participants recruited will be geographically located in the same precinct, with the same surgical staff seeing the same population catchment area and the only difference being the source of funding and reimbursement for surgery.

Ethics approval for the study was obtained from the Melbourne Health Human Research Ethics Committee in May 2015 (protocol reference 2015.035). The trial is being conducted in accordance with the Declaration of Helsinki and was registered on 16 September 2015 with the Australian and New Zealand Clinical Trials Registry (ACTRN12615000968572).

### Eligibility criteria

Eligible participants following cardiac surgery via median sternotomy at the participating centres will be invited to participate in the study. They will be identified through their admission to the cardiothoracic ward of both the public and private hospitals.

### Inclusion/exclusion criteria

Participants are eligible for the trial if they meet the following criteria:Adults undergoing isolated valve, coronary artery bypass graft (CABG) surgery or a combination of bothAble to provide informed consentAged 18 years and older

Participants are ineligible for the trial if they meet any of the following criteria:Insufficient English-language comprehensionReside outside the Melbourne metropolitan area (i.e., 52-km radius)

### Recruitment feasibility

We aimed to recruit 72 participants from among a pool of those admitted for surgery at each centre. Annually, approximately 650 sternotomy procedures are performed at RMH and 450 sternotomy procedures are performed at MPH. Therefore, recruitment of 72 participants is estimated to take 12 months with an average recruitment of 6 participants per week.

### Randomisation and allocation

Randomisation will be conducted by an independent person off-site using a computer-generated random 72 sequence numbering system (from 1 to 72) and a 1:1 allocation ratio. Concealment is via sealed, numbered, double-layered, opaque envelopes. Allocation occurs after baseline testing by opening of the next study envelope by a member of the staff of the university department of physiotherapy who is not involved in the study. The staff member then informs the treating physiotherapist of group allocation. The envelopes will be stored locked in a cabinet, and security measures are in place to prevent unblinding. To avoid allocation bias, Steps will be taken to limit authorised personnel (*n* = 2) with access/permission to open the study envelopes.

### Trial intervention

The implementation of the sternal precautions is performed by the same ward physiotherapist according to allocation for both groups. There will be a different physiotherapist for each participating hospital providing the intervention for both groups. Both physiotherapists are senior clinicians with over 5 years of clinical experience in cardiac surgery. Training will be provided by one independent physiotherapist to ensure consistency in each institution. Standard care is consistent across centres.

### Control group (standard care)

Whilst ‘standard care’ is not consistent in the literature cited previously [8, 13, 14, 24, 25], centres worldwide limit the use of the upper limbs for a minimum of 6 weeks [8, 13, 14, 24, 25]. The protocol we will apply is consistent across both institutions in this study. Therefore, consenting participants in the standard care group will receive the education and restrictive sternal precautions for the duration of 6 weeks. The sternal precautions will be delivered in both verbal and written formats by the treating physiotherapists as single individualised sessions for 15 minutes on the ward prior to discharge from the hospital. Patients will be instructed to adhere to the sternal precautions for the first 4–6 weeks post-operatively (Fig. 1a).

**Fig. 1 Fig1:**
[figure not shown]
**a** Control group (standard care) participant information flyer. **b** Intervention group (modified sternal precautions) participant information flyer. *S.M.A.R.T.* Sternal Management Accelerated Recovery Trial

The participants will be specifically instructed to do the following:Avoid pushing or pulling through the armsAvoid one-arm (unilateral) activityLimit the elevation of the arms to 90 degreesAvoid lifting objects heavier than 2 kgUse a cushion or perform sternal preservation technique (crossing the arms in a ‘self-hugging’ posture) when coughingLimit the use of the arms when transferring from sitting to standing and getting out of bedAvoid placing the arms behind the back

Participants will be advised not to continue tasks and/or exercises that are painful, to rest as required and to focus on a gradual return to their pre-surgery level of function.

### Intervention group

The modified sternal precautions will be delivered in both verbal and written formats by the treating physiotherapists as single individualised sessions for 15 minutes on the ward prior to discharge from the hospital. Patients will be instructed to adhere to the sternal precautions for the first 4–6 weeks post-operatively (Fig. 1b).

Participants in the intervention group will be specifically encouraged to do the following:Use pain and discomfort to guide the safe use of the armsAvoid pushing or pulling with one armUse both arms close to the body during liftingUse of arms is possible, but keep them close to the bodyAvoid stretching one or both arms backwards at the same timeUse a cushion or perform sternal preservation technique (crossing the arms in a ‘self-hugging’ posture) when coughing (same as above)When transferring, roll onto the side, ease the legs over the edge of the bed and carefully use the arms to sit up from a lying position

Pain and discomfort should be used to guide the safe limits of movement. The intervention pertaining to sternal management, including the type of sternal precautions, will be delivered in both verbal and written formats to each participant separately with a flyer developed specifically for the study to ensure standardisation. In both groups, all other aspects of patient care, including pre-operative management, general anaesthesia, intra-operative ventilation parameters, fluid delivery, prophylactic antibiotic prescription, pain management, use of lines and drains, general nursing care and discharge planning, will be provided at the discretion of nurses and physicians according to routine clinical practice at both hospitals.

### Intervention fidelity

Training will be provided for the two unblinded, dedicated staff to conduct the follow-up phone calls to ensure consistency in evaluating adherence to sternal precaution guidelines for the first 6 weeks after cardiac surgery. One staff member will evaluate the intervention group and another will follow the standard care group for both institutions. To minimise bias, the staff are required to encourage patients to continue with their allocated sternal management strategy using the standardised written instructions in addition to participants’ flyers. Participants will be informed that they will be contacted via telephone weekly to help reinforce their exercise and precaution guidelines for the first 6 weeks after cardiac surgery. Specifically, the standard care participants will be asked to follow the restriction on the use of their upper limbs and to limit the activities of their upper limbs and trunk during activities of daily living, bed transfers, and sit-to-stand manoeuvers. The intervention group will be encouraged to use their upper limbs bilaterally to perform activities of daily living, bed transfers and sit-to-stand manoeuvers. They will also be encouraged to perform upper limb exercise three times daily within the limits of pain and discomfort.

### Blinding

Patients, outcome assessors and data management are blinded to treatment allocation. Participants will be advised that they will be randomised to one of two groups of sternal precautions guidelines. The treating physiotherapist and nursing staff cannot be blinded to group allocation. The details of sternal management are not documented in the medical record. A blinded assessor located off-site from the hospital will assess all outcomes. Trial staff will conduct education sessions at set times on the ward that are on days separate from days scheduled for outcome assessment. If a treatment group participant informs the assessor of their post-operative education session, this will be noted and reported, and the reason will be entered when the randomisation is unblinded and analysed on an intention-to-treat basis.

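### The article claims patient blinding, but participants know the names of the two arms and are coached weekly in arm-specific behaviour, with nothing described to stop them recognising their arm

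*Protocol article*

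**What the plan says.** Patient blinding is asserted in four places in the protocol article:

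- The abstract describes a "double-blind, randomised controlled trial with concealed allocation, blinding of patients and assessors, and intention-to-treat analysis".
- Table 1 (registration data set) has "Masking: patient and assessor blinded".
- Trial design repeats that both patients and assessors are blinded.
- The Blinding section says "Patients, outcome assessors and data management are blinded to treatment allocation".

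What participants are told is described in two ways. Trial design says "Participants will be informed that they will be randomised to receive either standard or modified sternal precautions before hospital discharge". The Blinding section says "Participants will be advised that they will be randomised to one of two groups of sternal precautions guidelines", without the two labels.

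The treatment is a set of instructions. The Control group and Intervention group sections give each participant one 15-minute individual session on the ward, with verbal and written precautions and a flyer for that arm. Under Intervention fidelity, "Participants will be informed that they will be contacted via telephone weekly to help reinforce their exercise and precaution guidelines", over six weeks. In these calls "the standard care participants will be asked to follow the restriction on the use of their upper limbs", while intervention participants are encouraged to use both arms and to do arm exercises three times a day. The callers are unblinded, one for each arm.

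For the assessor, the Blinding section adds: "If a treatment group participant informs the assessor of their post-operative education session, this will be noted and reported".

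**The concern.** In this trial the treatment is behaviour that the participant must know and carry out. Someone who has heard that the options are standard and modified, and who is then coached for weeks either to restrict or to use the arms, has what is needed to work out which option was given. The article nevertheless states patient blinding without qualification.

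At stake is how the patient-reported results can be read. Pain, functional difficulty, fear of movement, quality of life and global change are rated by the participant, and a blinded interviewer cannot remove the influence of what the participant knows or expects. The TSK-11 and the FDQ are particularly close to the coaching: one measures fear of movement and the other rates difficulty with 13 arm and trunk tasks.

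A second, smaller matter is the disclosure rule. Assessor blinding depends partly on participants not revealing their instructions, and the questionnaires are given face-to-face. The rule for recording such a revelation is worded for a treatment group participant, although control participants also have an education session that they could mention.

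**Working it through.** No figure in the plan depends on this point, and the sample size is unaffected. The check sets the sections side by side, with one count and one comparison of dates.

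**1. Could a participant remain unaware of the arm?**

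| Step | Standard care | Modified precautions | Section |
|---|---|---|---|
| Told beforehand | Arms are standard or modified | Same | Trial design |
| Ward session | 15 minutes, individual, restrictive list | 15 minutes, individual, list permitting guided arm use | Control group; Intervention group |
| Written material | Arm-specific flyer | Arm-specific flyer | Fig. 1 caption |
| Weekly calls | Reinforce restriction | Encourage use of both arms, plus daily exercise | Intervention fidelity |

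The arms match in form (session length, flyer, calls) but differ in content, and the content is the treatment. The article describes no sham, no disguised labels and no other measure against recognition. The neutral wording in the Blinding section is not such a measure, because Trial design says that the labels are given.

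**2. Is the coaching in progress when the primary outcome is measured?** Calls run for the first 6 weeks after surgery. The 4-week visit has a window of ±14 days (Data collection): 28 − 14 = 14 days to 28 + 14 = 42 days, that is, weeks 2 to 6. The whole window lies inside the calling period. The 3-month visit comes after it has ended.

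**3. Which outcomes are exposed?** Table 1 lists seven key secondary outcomes: the cardiac pain tool, SF-MPQ-2, FDQ, grip strength, TSK-11, SF-36v2 and GRC. All but grip strength are self-reported: 7 − 1 = 6. The Secondary outcomes section adds the Sternal Instability Scale, which is a manual test, and an adherence questionnaire, which is self-rated. Counting those two gives 6 + 1 = 7 self-reported out of 7 + 2 = 9.

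**4. How exposed is the SPPB?** It consists of timed tasks scored with fixed cut-points. The assessor is off-site and blinded, education is given on days separate from assessment, and sternal management is not entered in the medical record. Participant effort remains a possible route for bias, but a narrower one.

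**5. What does the disclosure rule cover?** Elsewhere the arms are mostly called intervention or modified, and control or standard care. A treatment group participant is therefore most naturally someone in the intervention arm. The same section, however, uses treatment allocation and treating physiotherapist for both arms. The wording is ambiguous and leans towards one arm.

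**The case against.** The best defence is that the document does not show patients learning which label is theirs. The arms are alike in form, both are sets of precautions, they share the instruction on supporting the chest when coughing, and the Blinding section words the advice neutrally. The flyers are not reproduced in the text available. A participant could know the instructions without knowing whether they are the usual or the new ones.

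Part of this stands. That participants recognise their arm is an inference, though a strong one given that Trial design discloses both labels. What the defence could support is ignorance of the hypothesis, which differs from being blinded to allocation and is not what the article claims. Nor is this a matter of condensation in a journal article: the article states a property that its own procedures do not provide.

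Three stronger inferences are tempting, and the document does not support them:

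- *Control-arm disclosures were not recorded.* That depends on one reading of an ambiguous phrase.
- *The primary result rests on the assessor's blinding alone.* The separate education days, the absence of sternal management from the chart and the fixed timed scoring also protect it.
- *The self-reported outcomes are open-label in every respect.* The questionnaires are administered by a blinded assessor; it is the respondent who is not blinded.

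**Conclusion.** Patient blinding is not a property that the described design delivers. The trial is assessor-blinded, with participants who know the precautions they follow and can be expected to recognise the arm. This affects the interpretation of six of the seven key secondary outcomes in Table 1. The count shows exposure, not bias; neither the size nor the direction of any bias can be derived from the document. The primary outcome is less exposed, and no planned analysis or sample-size figure changes.

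The conclusion assumes that the Trial design account of what participants are told is the one that was used, and that the unseen flyers contain nothing that would disguise the arm. If participants heard only the neutral wording, recognition would be less certain, but the article would still need to say what they were kept unaware of.

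The disclosure rule is a wording fault that should be corrected. It is not proof that unblinding was monitored in one arm only.

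**What to change.** 1. In the abstract, Table 1, Trial design and Blinding sections, restate masking as assessor-blinded, with participants not blinded to the precautions received, and drop the term double-blind.
2. Reconcile Trial design and Blinding on what participants were told about the two arms.
3. In reporting, describe the cardiac pain tool, SF-MPQ-2, FDQ, TSK-11, SF-36v2 and GRC as rated by participants who were not blinded, though administered by a blinded assessor.
4. Reword the disclosure rule to cover a participant in either arm. Report recorded disclosures by arm, and state whether control-arm disclosures were captured.
5. Keep the intention-to-treat analysis as primary. Leaving out assessments with a disclosure would condition on an event after randomisation that may differ between arms, so it is not recommended as a remedy.

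Recruitment closed in November 2016 and follow-up ended in April 2017, so new disclosure data cannot be collected; item 4 is limited to what was recorded. The cost is some rewording and the loss of the double-blind label.
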